### Concurrent observational cohort

Potential participants who are excluded during the physical examination and eligible participants who decide to withdraw before randomisation will be asked to be part of a concurrent observational cohort inspired by the ﻿Spine Patient Outcomes Research Trial [50]. This cohort will be used to describe how excluded participants fare and which treatment they seek. If they agree to be in the cohort, they will receive the same questionnaires as the participants of the FIX-Heel Trial with the addition of a questionnaire about care-seeking behaviour and treatments received during the time between the last follow-up and the current follow-up. We will use the same follow-up times (4, 12, 26 and 52 weeks) as in the FIX-Heel Trial; however, all follow-ups will be conducted through e-mail.

### Patient and end-user involvement

To involve both patients and end users in designing the intervention, the participant leaflet was developed on the basis of semi-structured interviews with five patients with PF and five GPs. Patients were asked to describe their heel pain, how it had affected them and which topics they felt would be important to include in a leaflet and in advice to a patient in general. GPs were asked about their experience with the patient group, which treatments they would consider and which topics they felt would be important to include in a leaflet and in advice to the patient in general. The leaflet and fundamental patient advice that the physiotherapists will deliver orally to patients are a triangulation of the results of the interviews with both patients and GPs and recommendations from clinical guidelines and a systematic review [1, 6, 51].

We will invite representative participants from each group to be part of the future interpretation of the results. Their interpretation will be part of the dissemination of the results in the trial report and during conferences. In practice, we will invite two randomly selected participants of each group after the primary outcome has been collected. If a participant declines, we will randomly select a new participant from the same group.

### Sample size

The minimal clinically important difference of the FHSQ pain domain has been found to be either 12.5 or 14.1 points in this patient population [37, 52]. We have chosen the most conservative option (i.e., 14.1 points) to form the basis of the sample size calculation. Based on a standard deviation of 22 points, which is comparable to the overall standard deviations found in previous studies of this patient population [19, 53, 54], a two-sided 5% significance level, and a power of 90%, a sample size of 53 participants in each group will be necessary. Taking into consideration possible drop-outs, we will include 60 participants in each group, and thus the total sample size will be 180 participants.

### Statistical analyses

All statistical analyses will be performed by a blinded data analyst according to a pre-established analysis plan using the intention-to-treat principle. This plan is written in consultation with a statistician and will be published on the Aalborg University website before the inclusion of the last participant. SPSS software (IBM Corporation, Armonk, NY, USA) will be used as statistical software. We will use Q-Q plots and histograms to assess data normality. Missing outcome data will be imputed using multiple imputations based on the values from previous follow-ups, sex, age, and group allocation.

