## Methods

### Design and setting

The FIX-Heel Trial is designed as a randomised superiority trial with a three-group parallel design. Reporting of the protocol follows the Standard Protocol Items: Recommendations for Interventional Trials (SPIRIT) statement (checklist uploaded as Additional file 1), TiDieR (Template for Intervention Description and Replication checklist and guide) and the Consensus on Exercise Reporting Template for intervention description [31–33]. The preparation of the trial, including publishing this trial protocol, was done in accordance with the PREPARE trial guide [34]. Before the inclusion of the first participant, the trial was registered with ClinicalTrials.gov (NCT03804008). Patients will be recruited from general practice and via social media (see below). However, for pragmatic reasons, the information and training instructions will be given at the physiotherapy department at Aalborg University Hospital, and injections will be given at a private rheumatology clinic (ReumaNord) situated in Aalborg, Denmark. Participants will attend the baseline and 12-week follow-up appointments at the hospital, whereas a link to the questionnaires used will be sent via REDCap (Vanderbilt University, Nashville, TN, USA) to participants’ e-mail addresses for the 4-week, 26-week and 52-week follow-ups.

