### Randomisation and blinding

Participants will be stratified by sex and block-randomised in random concealed block sizes of 3 to 12 (1:1:1) in three parallel groups. A researcher not involved in the trial generated the allocation sequence using a random number generator on www.sealedenvelope.com and is the only person who knows the block sizes. The researcher was trained by the project manager in generating allocation sequences, and the process was piloted.

The randomisation is coded so that the project manager does not know which intervention is linked to which group number (group 1, 2 or 3). The envelopes will be kept in a locked room at Aalborg University Hospital where only the two physiotherapists involved in baseline testing have access. The randomisation schedule was prepared at the Center for General Practice at Aalborg University by a person not involved in the actual trial. The notes in the envelopes state both group number and intervention, and the physiotherapists responsible for assessing participants and delivering the interventions will not be aware of the coding before they open the first envelopes. In practice, after a participant has been enrolled, has filled out questionnaires, and has received initial patient advice and information regarding the practicalities of participation, the physiotherapist will take an envelope and assign the participant to the allocated treatment on the basis of randomisation.

The project manager will be responsible for performing the statistical analyses and will remain blinded to the coding until after the analyses have been performed. The analyses will be performed after the examination that includes the primary endpoint (the 12-week follow-up) of the last participant.

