### Interventions

#### Patient advice and heel cup

Participants in all three groups will receive the same initial fundamental patient advice and leaflet about their condition before randomisation. They receive brief information about pathology, risk factors and advice on how to decrease activities that lead to symptom flares and slowly progress back to former activity levels guided by symptoms. To ensure that all participants receive the exact same information, the physiotherapists read a written information out loud; however, they will ask control questions to clarify if the participants understand the information and allow participants to pose questions about the information and participation in general. The leaflet includes the same information that the physiotherapists deliver orally after inclusion in the trial.

Participants will be asked to refrain from seeking other treatments during the course of the trial. They will be allowed to self-treat their PF for pain relief (e.g., with ice or heat packs, rolling a tennis ball under the heel, or massaging the plantar fascia) if they have been doing this for at least 4 weeks prior to inclusion, but they will not be encouraged to do so. Participants will be handed a project diary in which they are asked to record any treatment that they may have received during the course of the trial, including any type of self-treatment and use of analgesic or anti-inflammatory substances. We will inform participants that follow-up on outcomes is critical, regardless of whether they comply with their allocated treatment. Two weeks after inclusion, the physiotherapist who included the participant will contact the participant to ask if they have any questions regarding the condition, the practicalities of participation, or in relation to performing the exercise depending on randomisation. If participants have not achieved a self-evaluated satisfactory result after 12 weeks, they may discuss other evidence-based treatments (e.g., plantar fascia stretching) with the physiotherapist, but they will be encouraged to continue to comply with their allocated treatment.

We will give all participants a silicone heel cup (Medi-Dyne Healthcare Products, Colleyville, TX, USA) for each shoe, and they are advised to use the heel cups whenever they are wearing shoes. If participants already use an insole or another type of foot orthosis, they are allowed to continue wearing this if they prefer this over the heel cups.

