#### Primary analysis

The primary analysis will investigate the between-group difference in FHSQ pain. We will use a linear mixed effects model with the participant as a random effect, and time (4, 12, 26 and 52 weeks), group allocation (PA or PAX or PAXI) and baseline value as fixed effects. Conclusions will only be drawn on the basis of the primary endpoint (12 weeks).

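### The stated imputation model for FHSQ pain is narrower than the primary mixed model: it omits week-26 and week-52 scores and, read literally, baseline pain

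*Protocol article*

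**What the plan says.** The Statistical analyses section of the protocol article gives a specific list of predictors: "Missing outcome data will be imputed using multiple imputations based on the values from previous follow-ups, sex, age, and group allocation". The Primary analysis section then sets up a linear mixed model with a random participant effect, whose fixed part is given as "time (4, 12, 26 and 52 weeks), group allocation (PA or PAX or PAXI) and baseline value as fixed effects". It confines conclusions to the 12-week endpoint.

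Three other places bear on how the imputation sentence should be read:

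- The section on the concurrent observational cohort refers to the "same follow-up times (4, 12, 26 and 52 weeks) as in the FIX-Heel Trial". Baseline is not listed as a follow-up.
- Under Design and setting, baseline and week 12 are hospital appointments, while a questionnaire link goes to "participants’ e-mail addresses for the 4-week, 26-week and 52-week follow-ups".
- Under Randomisation and blinding: "The analyses will be performed after the examination that includes the primary endpoint (the 12-week follow-up) of the last participant".

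**The concern.** An imputation model should contain at least the variables of the analysis it feeds. Here it does not. A participant who misses the week-12 hospital visit but answers the e-mailed questionnaires at weeks 26 and 52 is imputed as if those answers did not exist. If week 4 is missing too, the literal wording leaves only sex, age and group, although the participant completed questionnaires before randomisation.

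The pattern is plausible in this trial. Week 12 requires attendance and the later visits do not. Participants are also told that "follow-up on outcomes is critical, regardless of whether they comply with their allocated treatment". Differences in missingness between arms are plausible as well, because participants know their allocation and the Discussion acknowledges that treatment burden differs between arms.

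The comparison at stake is the only one from which conclusions are drawn. Imputed values too weakly tied to the omitted scores cost precision. If missingness follows those scores differently by arm, they also shift the contrast.

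**Working it through.** **The plan's own figure.** Inputs from Sample size: difference 14.1, SD 22, two-sided 5%, power 90%. The normal approximation gives n = 2 × (22 × (1.960 + 1.282) / 14.1)² = 51.2, so 52 per group. The t-test calculation gives 89.9% power at 52 and 90.5% at 53, so the stated 53 is reproduced. Going from 53 to 60 allows for 7/60 = 11.7% loss. The article states no rate.

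**Scores available for a missing week-12 value.**

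| Source | Primary model | Imputation, as worded |
|---|---|---|
| Baseline | yes | no, read literally |
| Week 4 | yes | yes |
| Week 26 | yes | no |
| Week 52 | yes | no |

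**Information lost (assumed correlations).** With k predictors and equal correlation ρ, R² = kρ² / (1 + (k − 1)ρ). At ρ = 0.5, week 4 alone gives 0.25, and baseline with weeks 4, 26 and 52 gives 4 × 0.25 / 2.5 = 0.40. With first-order autoregressive correlation 0.7, week 4 alone gives 0.7² = 0.49, and all visits give 2 × 0.49 / 1.49 = 0.66.

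**Bias (simulation).** Settings: 60 per group, SD 22, 10 imputations, 800 runs per scenario, baseline-adjusted week-12 contrasts against PA. Assumptions not in the documents: correlations of 0.4 to 0.5 (exchangeable) or 0.7 (autoregressive), log-odds slope of 1 per SD for missingness, and weeks 26 and 52 fully observed. The table gives the size of the mean shift from the complete-data estimate under the wording as written.

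| Missingness depends on | 11.7% missing | 20% missing |
|---|---|---|
| nothing, or baseline or week 26 equally in all arms | about 0 | about 0 |
| baseline, opposite directions by arm, exchangeable | 0.9–1.0 | 1.6 |
| the same, autoregressive | about 0 | about 0 |
| week 26, in PA only | 0.7–1.0 | 1.1–1.6 |
| week 26, opposite directions by arm | 1.2–1.7 | 2.0–2.8 |

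The sign follows the direction of selection: mirrored selection gives a shift of similar size the other way. In the last row, adding baseline alone still leaves 1.0–1.8 and 1.6–2.8. Adding baseline and both later visits brings every scenario to at most 0.12, close to simulation error.

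**What such a shift means.** The standard error at 53 per group is 22 × √(2/53) = 4.27, and power is Φ((14.1 − s)/4.27 − 1.96) for a shift s against the treatment:

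- s = 0: Φ(1.34) = 91%
- s = 1: Φ(1.11) = 87%
- s = 1.7: Φ(0.94) = 83%
- s = 2.8: Φ(0.68) = 75%

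A shift of the opposite sign would instead exaggerate the difference.

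**Later scores at the analysis date.** Trial status gives 96 participants by 5 October 2019 and recruitment ending in July 2020. Adding 84 days to 1–31 July puts the last week-12 visit between 23 September and 23 October 2020. Going back 364 days, week 52 is reached by those enrolled by 25 September to 25 October 2019, so roughly the first 96 of 180 (53%). Going back 182 days, week 26 is reached by those enrolled by 25 March to 24 April 2020. Later scores would therefore exist for part of the sample only. In a separate check of a similar adverse scenario, with later visits available for an assumed 60%, about 0.4 to 0.8 points of bias remained after the fix.

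**The case against.** The sentence is one line in a condensed article that defers to an analysis plan not shown here. That would excuse silence on the predictors, but the article names them, and a plan that follows it inherits the restriction.

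Four other objections carry more weight.

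- **Baseline may have been intended.** It is a covariate in the primary model and was collected before randomisation. A reader might infer that baseline is deliberately excluded. The wording permits that reading but does not establish it, so this part is a request for clarification. The omission of weeks 26 and 52 does not depend on it.
- **The 11.7% is an allowance for drop-outs.** Permanent drop-outs have no later scores, so only baseline can help them. With loss after week 4 driven by week-4 pain, imputing from earlier values is valid: a large-sample check, with that dependence in opposite directions by arm, gave a bias of 0.0. Those who miss week 12 and return are a subset whose size the documents do not give.
- **Later data will be incomplete at the stated analysis date.** This stands. It limits what the fix achieves but does not justify ignoring the scores that exist.
- **The larger figures need special conditions.** Missingness must track the omitted score differently by arm. The simulation also analysed week 12 by baseline-adjusted regression and did not run the full sequence of imputation followed by the mixed model.

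**Conclusion.** The point holds as a moderate, conditional weakness in a stated method. The imputation model is narrower than the analysis model: on any reading it leaves out weeks 26 and 52, and literally it leaves out baseline. Information is lost for participants who miss week 12 and answer later. Bias arises only if missingness differs by arm and relates to the omitted values.

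Under the assumptions listed, with arm-differential missingness related to week 26, the shift is about 0.7 to 1.7 points at 11.7% missing, or 5% to 12% of the 14.1-point target (0.7/14.1 and 1.7/14.1). The extreme case, 2.8 points or 20%, required 20% missing and week-26-driven missingness in opposite directions by arm. If missingness does not differ by arm, the shift is near zero.

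Two stronger inferences are tempting. One is that the plan as written will bias the primary result by nearly 3 points. The documents give no missingness rate, pattern or correlation to support that. The other is that using all visits would remove the bias entirely. That holds only with later scores fully observed, which the stated analysis date does not provide.

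**What to change.** Replace the list of predictors with one that includes baseline FHSQ pain and all FHSQ pain scores available at the analysis date (weeks 4, 12, 26 and 52), plus sex, age and group. Alternatively, fit the primary mixed model to the observed data by likelihood, which already uses baseline and every observed visit, and keep multiple imputation as a sensitivity analysis.

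Reconcile this with the analysis timing under Randomisation and blinding. State whether the primary model will be fitted once the last week-12 visit is complete, with partial week-26 and week-52 data, or after full follow-up. If the earlier date stands, acknowledge that the change reduces the possible bias but may not remove it, and report week-12 missingness by arm, separating participants who later returned from permanent drop-outs.

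The cost is a sentence or two in the analysis plan. No new data are needed.

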#### Primary analysis

The primary analysis will investigate the between-group difference in FHSQ pain. We will use a linear mixed effects model with the participant as a random effect, and time (4, 12, 26 and 52 weeks), group allocation (PA or PAX or PAXI) and baseline value as fixed effects. Conclusions will only be drawn on the basis of the primary endpoint (12 weeks).

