#### Primary outcome

The primary outcome is the mean pain domain score of the FHSQ at the 12-week follow-up. The FHSQ is a questionnaire ranging from 0 (worst possible score) to 100 (best possible score) with high reliability (ICC, 0.74–0.92) that assesses multiple dimensions of foot-related health and function and is recommended in this patient population [35, 36]. The minimal clinically important difference of the pain domain is 14.1 points [37]. We will use a Danish validated translation of the original questionnaire [38].

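### A participant random effect with a single residual variance would give the week-12 contrast a standard error averaged over four visits; an unstructured covariance avoids this at almost no cost (optional improvement)

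*Protocol article*

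**What the plan says.** The primary analysis section of the protocol article specifies the model in one sentence. The within-participant part is "We will use a linear mixed effects model with the participant as a random effect"; the fixed part is "time (4, 12, 26 and 52 weeks), group allocation (PA or PAX or PAXI) and baseline value as fixed effects". No residual covariance and no group-by-time term are mentioned. The section closes with "Conclusions will only be drawn on the basis of the primary endpoint (12 weeks").

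The outcome is the FHSQ pain score, "ranging from 0 (worst possible score) to 100 (best possible score"). The sample size section uses a single SD: "Based on a standard deviation of 22 points, which is comparable to the overall standard deviations found in previous studies of this patient population". No SD or correlation by visit appears anywhere in the article.

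The statistical analyses section refers to a separate analysis plan, which is not at hand: "This plan is written in consultation with a statistician and will be published on the Aalborg University website before the inclusion of the last participant". It also says that missing outcomes will be multiply imputed.

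**The concern.** A participant random effect plus one residual variance is compound symmetry. It assumes the same variance at all four follow-ups and one common correlation between any two of them. Equal variance is a doubtful assumption for a bounded score followed through recovery. Scores may bunch towards 100 as patients recover, or spread out if some recover and others do not. The Background describes both courses: a historical expectation that 80% are symptom-free within 12 months, and a trial in which 40% still had symptoms at 2 years. The patient advice section also lets participants who are dissatisfied after 12 weeks discuss other treatments, so weeks 26 and 52 may be observed under different conditions from week 12.

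All three superiority hypotheses are judged at week 12. If week-12 scores vary more than the four-visit average, the confidence interval is too narrow and false claims of superiority exceed 5%. If they vary less, the interval is too wide and power is lost. Either way, visits on which no conclusion is drawn would set the precision of the one visit that matters.

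**Working it through.** **1. The plan's own figure.** Inputs from the sample size section: difference 14.1, SD 22, two-sided 5%, power 90%.

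Normal approximation: n = 2 × [22 × (1.960 + 1.282) / 14.1]² = 51.2, so 52 per group. With the noncentral t distribution, power is 0.8992 at 52 and 0.9047 at 53. The stated 53 per group is reproduced.

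**2. Which variance the week-12 contrast uses.** Assume a random intercept, independent equal-variance residuals, group-by-visit terms and complete data. Multiple imputation makes each completed data set balanced, so the balanced algebra applies. Let S be the pooled within-group 4 × 4 covariance matrix of the visits:

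- between-participant mean square: MSB = (sum of all elements of S) / 4
- within-participant mean square: MSW = (trace of S − MSB) / 3
- model's total variance: (MSB + 3 × MSW) / 4 = trace(S) / 4

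The total is the plain mean of the four visit variances. The off-diagonal elements cancel, so unequal correlations do not affect this standard error; only unequal variances do.

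**3. Size.** Let V be the mean visit variance and s the week-12 SD.

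- model SE = √(2V/53); correct SE = s × √(2/53)
- k = √V / s
- type I error = 2 × [1 − Φ(1.96k)]
- power = Φ(14.1 / correct SE − 1.96k)

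At s = 22 the correct SE is 22 × √(2/53) = 4.27, and power with the week-12 variance is 0.910. The SD patterns below are assumptions. Strictly they are SDs after baseline adjustment, but k depends only on their ratios.

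| SD at weeks 4/12/26/52 | V | √V | k | Type I error | Power |
|---|---|---|---|---|---|
| 22/22/22/22 | 484 | 22.00 | 1.000 | 5.0% | 0.910 |
| 24/22/20/18 | 446 | 21.12 | 0.960 | 6.0% | 0.922 |
| 18/22/24/26 | 515 | 22.69 | 1.032 | 4.3% | 0.899 |
| 18/22/25/27 | 540.5 | 23.25 | 1.057 | 3.8% | 0.890 |
| 22/22/18/16 | 387 | 19.67 | 0.894 | 8.0% | 0.939 |
| 20/22/18/14 | 351 | 18.73 | 0.852 | 9.5% | 0.948 |
| 22/22/26/28 | 607 | 24.64 | 1.120 | 2.8% | 0.865 |
| 16/18/24/26 | 458 | 21.40 | 1.189 | 2.0% | 0.956 |

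In the last row the week-12 SD is 18, so the comparison power with the correct variance is 0.981. Where type I error exceeds 5%, the higher power is not a gain; it comes from an interval that is too narrow.

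**4. Check by simulation.** With 20,000 null runs per pattern, three groups of 53, lag correlation 0.7 and no baseline covariate, type I error under the pooled variance was 7.8% (22/22/18/16), 9.3% (20/22/18/14), 4.0% (18/22/25/27) and 2.0% (16/18/24/26). With a week-12-specific variance it was about 5% in each.

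**5. The fixed effects exactly as listed.** Without a group-by-time term there is one group effect for all four visits. In the same four patterns its random-intercept test held 5.0%, 5.2%, 5.3% and 5.0%. But it estimates an average over visits, not week 12. If the true differences were 20, 14.1, 5 and 0, it would estimate (20 + 14.1 + 5 + 0) / 4 = 9.8 points.

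**The case against.** The strongest case against has four parts.

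- **The article is silent on residual covariance.** A participant random effect can be combined with a structured residual covariance, and a condensed article may leave that to the announced analysis plan. This stands. A reader might infer that the article forces compound symmetry, or excludes any other structure; its text does not say so.
- **The model as listed holds its 5% level.** This is correct (step 5) and limits the point. It does not remove it, because the listed model yields no week-12 contrast and the stated conclusion needs one. Once the group-by-time term is added, the pooling in step 2 follows.
- **The sizes rest on chosen SD patterns.** This stands. Both patterns that push type I error to 8% or more have their largest SD at week 12 (in one, tied with week 4). The largest distortion, 19%, assumes a week-12 SD of 18 where the protocol plans on 22, and power there is still about 96%. The Background reports proportions with symptoms, not score variances.
- **Unequal spacing of visits and fading correlation do not bias this standard error when data are complete.** This also stands, so neither is offered here as a cause.

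What remains is a stated structure that suits inference at a single visit poorly, for which a better one is available at almost no cost.

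**Conclusion.** The point holds as a conditional one of low severity. If the model is fitted as plainly read and a week-12 contrast is taken from it, the standard error reflects the average variance of four visits. With equal visit SDs nothing is lost. Under the assumed steady trends around 22 the error is 3-4% of the standard error, with type I error of 4.3% or 6.0%. Under the stronger assumed patterns it reaches 11-19%, with type I error from about 2% to 9.5%. The sign cannot be known in advance. These figures assume 53 per group, complete or imputed data, and independent equal-variance residuals.

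A reader might infer that the trial's false-positive rate is inflated. The documents do not support that: they give no SD by visit, the error may be conservative or nil, and the unseen analysis plan may already specify another covariance.

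**What to change.** State the primary model as a repeated-measures model for weeks 4, 12, 26 and 52, with visit as a category, group-by-visit terms and the baseline score. Use an unstructured covariance over the four follow-ups in place of the participant random effect, fitted by REML with Satterthwaite or Kenward-Roger degrees of freedom. Name heterogeneous compound symmetry as the fallback if the model does not converge. Read the three pairwise group contrasts at week 12. If the separate analysis plan already does this, a sentence confirming it is enough. The same structure can serve the continuous FHSQ and PSEQ secondary outcomes, over the visits at which each is measured.

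The cost is about one sentence. Four visits need 4 × 5 / 2 = 10 covariance parameters, which is routine with 180 participants. No extra data and no added patient burden are involved.

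### Randomisation is stratified by sex, but the primary mixed model as listed leaves sex out, which makes the test slightly conservative if sex is prognostic (minor)

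*Protocol article*

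**What the plan says.** Under Randomisation and blinding, the protocol article states: "Participants will be stratified by sex and block-randomised". Allocation is 1:1:1 with concealed, randomly varying block sizes, and sex is the only stratification factor named.

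Under Primary analysis, the model is a "linear mixed effects model with the participant as a random effect". Its fixed effects are time (4, 12, 26 and 52 weeks) together with "group allocation (PA or PAX or PAXI) and baseline value as fixed effects". Sex is not in that list. The same section confines inference to one visit: "Conclusions will only be drawn on the basis of the primary endpoint (12 weeks").

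Sex appears once in the analysis sections, under Statistical analyses, where missing outcomes are imputed "based on the values from previous follow-ups, sex, age, and group allocation". The article does not say that the primary comparison will be adjusted for sex, and it gives no reason for leaving sex out.

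**The concern.** Stratified blocks keep the sexes nearly balanced across arms, so the estimated treatment difference hardly varies through chance imbalance in sex. A model without sex does not know this. It leaves the between-sex variance in the residual and computes the standard error as if sex could fall unevenly between arms. If sex is prognostic given the baseline score, the reported standard error is then larger than the real spread of the estimate. Confidence intervals are somewhat too wide, and the true test size falls somewhat below 5%.

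This is not a detail left open for the separate analysis plan. The article names the fixed effects, and the list does not follow the design. At stake is the calibration of the 12-week comparisons on which all three superiority hypotheses are judged.

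**Working it through.** **Inputs.** From Sample size: difference 14.1 points, SD 22, two-sided 5%, power 90%, 53 per group (60 recruited). From Randomisation and blinding: stratification by sex, 1:1:1. Assumed, because the documents give no figure: sex explains a share R² of the residual variance at 12 weeks, with R² between 1% and 5%. The SD of 22 is taken as the residual SD of the model without sex. The formulas treat the 12-week contrast as a two-group comparison.

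**The plan's own figure.** n per group = 2 × (22/14.1)² × (1.960 + 1.282)² = 51.2, so 52. The t-based solution is 52.14, so 53. The stated 53 reproduces. It rests on an SD with no adjustment for sex, so omitting sex does not make it wrong.

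**What R² means in points.** R² = p(1 − p)d²/22², where d is the sex difference given baseline and p the share of one sex. With p = 0.5, R² = 1% corresponds to d = 4.4 points and R² = 5% to d = 9.8 points.

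**Standard error.** The model without sex reports a value proportional to 22. The true sampling SD under stratification is proportional to 22√(1 − R²). The overstatement is 1/√(1 − R²) − 1:
- R² = 1%: 1/0.9950 − 1 = 0.5%
- R² = 5%: 1/0.9747 − 1 = 2.6%

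**Type I error without sex** = 2 × [1 − Φ(1.960/√(1 − R²))]:
- R² = 1%: 2 × [1 − Φ(1.970)] = 4.9%
- R² = 5%: 2 × [1 − Φ(2.011)] = 4.4%

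**Power at 14.1 points, 53 per group.** The reported SE without sex is 22 × √(2/53) = 4.274, and 14.1/4.274 = 3.299. With R² = 0, power = Φ(3.299 − 1.960) = 91.0%.
- Without sex: Φ((3.299 − 1.960)/√(1 − R²))
- With sex: Φ(3.299/√(1 − R²) − 1.960)

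| R² | Without sex | With sex |
|---|---|---|
| 1% | Φ(1.346) = 91.1% | Φ(1.356) = 91.2% |
| 5% | Φ(1.374) = 91.5% | Φ(1.425) = 92.3% |

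The gain is less than 0.2 percentage points at 1% and about 0.8 at 5%.

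**Simulation check.** The simulation used sex-stratified permuted blocks of 3, 6, 9 or 12, 180 participants, 70% of one sex (assumed), total SD 22 and no treatment effect. The 12-week outcome was analysed alone, with 20,000 runs per row.

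| Sex difference (assumed) | Mean reported SE, sex omitted | True SD of that estimate | Type I error, sex omitted | Mean SE, sex included | Type I error, sex included |
|---|---|---|---|---|---|
| 0 | 4.01 | 4.03 | 5.0% | 4.01 | 5.0% |
| 5 | 4.01 | 4.01 | 4.9% | 3.99 | 5.0% |
| 10 | 4.01 | 3.93 | 4.7% | 3.92 | 5.2% |
| 14.1 | 4.01 | 3.82 | 4.2% | 3.84 | 5.1% |

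The Monte Carlo error of each type I rate is √(0.05 × 0.95/20,000) = 0.15 points. The direction agrees with the formulas. At a 5-point sex difference the effect cannot be told apart from zero.

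**The case against.** The strongest counter-argument is that stratification itself delivers the precision, whether or not sex is modelled. That stands. In the simulation, the true SD of the estimate without sex (3.93 and 3.82 at 10 and 14.1 points) is essentially the SE of the model with sex (3.92 and 3.84). What is misstated is the reported standard error.

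A reader might infer a larger power loss by comparing 91.0% (SD 22) with 92.3% (SD reduced for R² = 5%), a gap of 1.3 points. That comparison holds power without sex fixed. In a sex-stratified trial it also rises with R², to 91.5%, so the gain from adding sex is 0.8 points.

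The harm is also conditional. It needs sex to predict pain beyond the baseline score, which the model already contains, and no section supports a value. If sex has no such effect, the two models agree. This also stands, which is why the size is given only as a range under an assumption.

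Two further inferences fail:
- **Sex in the imputation but not in the analysis.** This is not a defect, because an imputation model may hold more predictors than the analysis model. Age is in the same position.
- **The secondary continuous models.** Secondary analyses names linear mixed models without listing fixed effects, so nothing is misstated there.

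**Conclusion.** The point holds as a minor one. The listed fixed effects of the primary model omit the only stratification factor, and the article gives no reason. If sex is prognostic beyond baseline, the consequence is conservative: intervals slightly too wide and a test size slightly below 5%. Under the assumed 1% to 5% of residual variance the effect is small on every measure, with less than one percentage point of power at stake.

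The documents do not support reading this as bias, an inflated type I error, an inadequate sample size or a material loss of precision. The omission itself is certain from the text. The size of its effect depends wholly on an assumption about sex that the documents do not inform.

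**What to change.** Add sex as a fixed effect in the primary mixed model, alongside time, group and baseline value. Use the same covariate in the linear mixed models for the secondary continuous outcomes, for consistency rather than to correct an error there.

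Specify this before the analysis plan is published, which the article places ahead of the last inclusion (96 of 180 were included at submission). The adjustment is then pre-specified and not chosen after seeing results. If the separate plan, which is not at hand, already names sex, a note that it supersedes the article's list is enough.

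The cost is one degree of freedom. Sex is known for every participant at randomisation, so no new data are needed and the sample size does not change.
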